##### Fidelity

Face-to-face coached-based MEI visits will be recorded. A standardized fidelity checklist will be utilized by the supervising psychologist to quantify discussion of topic domains, rating the domains on a 3-item Likert scale (0=none, 1=partial discussion, and 2=focused discussion) with provided anchors. The domains for coverage during an MEI coach visit are (1) taking medication as prescribed, (2) attending medical appointments, (3) experience at the health provider’s office, (4) encouraging participants’ use of the MEI mobile app, (5) participant’s actual engagement with the mobile app, (6) alcohol or drug use, (7) sexual health, and (8) role of values in participants’ health decision making. A total of 20% of all recorded visits will be reviewed for overall fidelity, seeking a representative sample across MEI coaches, and follow-up visits (eg, baseline and 3-months) across the course of the study. Interrater reliability will be conducted by a coworker of the supervising psychologist trained in the intervention and research methods. MEI coaches will also complete their own fidelity assessment after each MEI coach face-to-face visit, which will help to regularly refresh and reinforce the core elements of each study visit. Data will also be collected from study participants about what topics were covered in their study visits. MEI coaches will also log all study contact with each participant on a secured study record, allowing for monitoring and feedback on the frequency of telephonic encounters.

#### Coach-Based MEI for Youth at Risk for HIV

The third aim is to use an RCT to examine the efficacy of a mobile-enhanced coach-based intervention to achieve uptake of and adherence to PrEP and other preventive behaviors (eg, *protected* sex acts) among youth at elevated risk of HIV infection.

#### Aim 3

##### Study Sample

This sample will be composed of YBLMSM or YBLTW recruited into aim 1, who test negative for HIV but are not currently on PrEP, and report either engaging in condomless anal intercourse or a prior history of a sexually transmitted infection. Additional eligibility includes no plan to relocate in the next 18 months; not enrolled in another PrEP behavioral intervention; and currently own or have access to a cell phone, private tablet, or laptop. Potential participants are provided information about the study and must consent to participate. We aim to recruit 225 YBLMSM or YBLTW at risk for HIV.

##### Study Procedures

After enrollment, participants complete a baseline survey and are randomized (1:1) to 1 of 2 study arms: coached-based MEI or SOC. Randomization to the intervention arms is stratified by site; age group, to yield a balanced randomization between younger (aged 15-19 years) and older (aged 20-24 years) age groups; and the enrollment city. After each participant is identified, they are provided with their assigned treatment assignment.

### SOC

Participants randomly assigned to the SOC arm in the at risk for HIV group receive a similar structure as those with uncontrolled HIV. Initially, they are provided information about HIV prevention strategies and the schedule for follow-up data assessments. During quarterly meetings, a brief check-in conversation and active listening is conducted without the use of SBIRT, MI, or goal-setting, and participants are referred, if needed, to local clinical or community assistive and services at each follow-up visit.

### MEI Coach Intervention

The focus of the Providing Unique Support for Health (PUSH) study is to engage individuals at risk for HIV into prevention and care. The approach is the same as aim 2, modeled after life steps [12,87,88] and based on the case management protocol 078 of the HPTN [82]. It is tailored to the prevention needs of the youth. As such, during the first step, the coach uses MI to orient participants and increase their readiness for preventive engagement. The counseling session addresses psycho-education about HIV risk; planning and problem-solving for mitigating risk, including addressing coexisting substance use; coping with side effects and adherence of PrEP; and/or other participant concerns, developing a plan to address slips in PrEP adherence (if applicable) or condom use. Coaching is tailored to the participants’ specific needs and case management or navigation needed. As with the second aim, randomly assigned participants will be requested to meet with their MEI coach every 3 months and have weekly telephonic check-ins, to review progress on personal goals, risk reduction, and help to troubleshoot factors that may increase HIV risk or personal goals. The MEI coach will utilize MI, SBIRT, active listening, and goal-setting in face-to-face visits, and telephonically will check-in on their lives, their goal progress, and app usage. MI strategies will be utilized to address motivational and situational barriers to study engagement in person or telephonically (Table 1).

Similar to the second aim, this MEI coach intervention focuses on 3 steps in the support process: MyCare (Steps 1 and 2) and MyHealth (step 3). MyCare (Step 2) adds to this evidence-based approach by recognizing that uptake of PrEP or prevention services is a personal choice grounded in a variety of behavioral and psychosocial domains. MyHealth is based on the premise that a patient engaged in self-management and supportive strategies will feel empowered to take ownership of their own health care needs. The MEI coach will determine the participant’s desire for support and the frequency and schedule of messages. For example, some participants embrace engagement intermittently, whereas other participants delay engagement and need to be taken through the engagement steps again. Participants are provided with as much or as little coaching as needed using this flexible approach, but the MEI coach will check-in with participants telephonically weekly (at a minimum), and participants are requested to attend face-to-face follow-up coach visits at 3, 6, and 12 months. During these visits, the coach will review participant’s progress toward personal and health goals, motivate and reinforce treatment engagement, review substance and risk reduction goals, and help problem-solve any obstacles that may have arisen. Using this approach, the participant is thus empowered to take the lead with recommendations and guidance from the MEI coach. Participants receive ongoing screening for sexual risk and substance use, and the coach’s approach is modified based on self-reported needs.

The study infrastructure for supporting and maintaining the MEI coach will be duplicated for the third aim. MEI coaches will receive remote bi-weekly support, instruction, troubleshooting, and feedback from the supervising psychologist, focusing on the delivery of MI, goal-setting, and SBIRT. Audiotaped recordings will be conducted during face-to-face visits, with the informed consent of the participant and discretion of the MEI coach, and will be reviewed by the supervising psychologist for feedback and assistance to the MEI coach and to track study fidelity. Likewise, participants and MEI coaches will complete fidelity assessments postvisit to reinforce study aims, prevent intervention drift, and provide additional data about the intervention delivered.

#### Data Collection for Aims 2 and 3

The PUSH study uses a built-in randomization engine adapted from previous studies [89]. The allocation between intervention and control arms is determined randomly by the engine, where each round comprises 2 intervention and 2 control assignments that are linked to the stratification factors of site and age group. Once a round is completed, a new round begins.

Participants are asked to participate in research visits at 0, 3, 6, 9, 12, and 18 months (exit interview). This visit schedule aims to ensure frequent contact and to minimize attrition. Laboratories and study-related activities are described in Table 2. Surveys provided at baseline (Textbox 1) are re-administered at each follow-up with additional questions focused on ART, PrEP, barriers, and facilitators to adherence.

**Table 2 table2:** Study visits and associated laboratory tests.

Tasks	Visits					
	Baseline	3 months	6 months	9 months^a^	12 months	18 months
Complete a survey	✓^b^	✓	✓	✓	✓	Exit interview
Provide blood for HIV-1 RNA viral load testing (aim 2) or HIV-1 antibody testing (aim 3)	✓	✓	✓	—^c^	✓	—
Provide urine for drug testing	✓	✓	✓	—	✓	—
Update locator information	✓	✓	✓	✓	✓	—
Meet with MEI^d^ coach (intervention only)	✓	✓	✓	✓	✓	✓
Medical chart review (research staff only)	✓	✓	✓	✓	✓	✓
Compensation, US $	50	50	50	10 check-in via phone; 25 survey	50	25
Participate in an in-depth interview (selected participants)	✓	—	✓	—	✓	—
Compensation, US $	25	—	25	—	25	—

^a^9-month visit constitutes either a brief phone check-in (5 min) or in-person survey (15 min).

^b^Data collected at this time point.

^c^Data not collected at this time point.

^d^MEI: mobile-enhanced intervention.

#### Sample Size Considerations

We aim to recruit up to 2000 YBLMSM and YBLTW to be screened for eligibility for aims 2 and 3. We conservatively estimate that 15.00% of the RDS recruited sample will be HIV-infected and not virally suppressed, given an HIV prevalence of 25% to 40% among YBLMSM and YBLTW across the sites and as many as 60% of HIV-infected YBLMSM are undiagnosed [4,9].

We expect a 15.0% loss to follow-up over 1 year in aim 2. Starting with n=240 will yield an effective sample size of 204 individuals in total, or 102 in each group, available for analysis in aim 2. A total estimate of n=200 will be enough to detect an average increase in the viral suppression proportion over the 3 follow-up visits of 16.0% from 24.0% assumed in the control arm to 40.0% in the coached-based MEI arm (odds ratio, OR 2.03), assuming a power of 85.0%. We expect a slightly greater loss to follow-up (20.0% loss to follow-up) in participants in aim 3. Starting with n=225 will yield an effective sample size of 180 individuals in total or 90 in each group. We estimate that a total of 180 participants (90 per group), and assuming a 15.0% average rate on PrEP in the control arm, we can detect an average increase of 14.0% to 29.0% (OR 2.31) with power 85.0%. Lost to follow-up estimates are based on the team’s prior work with this population.

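### The aim 2 detectable effect is stated two incompatible ways: 24.0% versus 40.0% is an odds ratio of 2.11, not the printed 2.03

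*Protocol article*

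**What the plan says.** All the figures are in the Sample Size Considerations section of the protocol article.

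- **Aim 2 (viral suppression).** The detectable gain, averaged over three follow-up visits, is given as one "of 16.0% from 24.0% assumed in the control arm to 40.0% in the coached-based MEI arm (odds ratio, OR 2.03"). The percentages and the odds ratio thus stand in the same sentence. On size, it says: "A total estimate of n=200 will be enough to detect an average increase in the viral suppression proportion". The power is given as 85%. The 200 is slightly below the 204 left after the 15% loss applied to 240 participants.
- **Aim 3 (PrEP use).** The control rate is 15.0%, with 180 analysable participants, and the text says "we can detect an average increase of 14.0% to 29.0% (OR 2.31) with power 85.0"%.

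The section gives no significance level, sidedness or within-person correlation for either aim.

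**The concern.** An odds ratio is fixed once the two proportions are given, so a sentence that prints both can be checked with no further assumption. Here they do not match. Viral suppression is the aim 2 primary outcome, so the effect that the trial claims to be able to detect has two values: 16.0 points, or about 15.1 points.

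The 85% power at 200 participants can belong to only one of them. Anyone who later judges the result against the planned effect, or reuses the calculation, would have to guess which. Either 2.03 is a misprint and the power is untouched, or 2.03 was the input and the printed 40.0% and 16.0 points are not the effect for which 85% was computed.

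**Working it through.** **1. Odds ratios from the printed percentages.** OR = [p2/(1 − p2)] / [p1/(1 − p1)].

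- Aim 3: (0.29/0.71)/(0.15/0.85) = 0.4085/0.1765 = 2.31. This agrees with the plan, so the ordinary definition was used.
- Aim 2: (0.40/0.60)/(0.24/0.76) = 0.6667/0.3158 = 2.11. The plan prints 2.03.

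**2. Can rounding or another measure explain 2.03?**

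- The percentages are printed to one decimal. The extremes are 24.05% versus 39.95%, which gives 2.10, and 23.95% versus 40.05%, which gives 2.12. The value 2.03 lies outside.
- The risk ratio is 0.40/0.24 = 1.67, which is not 2.03 either.

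**3. What 2.03 would mean.**

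- From 24.0%: odds = 2.03 × 0.3158 = 0.6411, so p2 = 0.6411/1.6411 = 0.391. The difference is 39.1 − 24.0 = 15.1 points.
- Keeping 40.0%: control odds = 0.6667/2.03 = 0.3284, so p1 = 0.3284/1.3284 = 24.7%, not 24.0%.

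**4. What the ambiguity could do to power (illustration only).** Assumptions that the document does not state: two-sided 5% test, two-proportion comparison with pooled variance under the null, exchangeable correlation ρ. The plan gives three visits for aim 2, and n = 200 means 100 per arm. The effective number per arm is n_e = 100 × 3/(1 + 2ρ), and with p̄ the mean of p1 and p2,

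power = Φ{[(p2 − p1)√n_e − 1.96√(2p̄(1 − p̄))] / √(p1(1 − p1) + p2(1 − p2))}.

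For each candidate effect, solve for the ρ that gives 85%, then apply that ρ to the other effect:

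| 85% computed for | ρ needed | n_e per arm | Power at the other effect |
|---|---|---|---|
| 24.0% vs 40.0% | 0.49 | about 151 | about 81% at OR 2.03 (39.1%) |
| 24.0% vs 39.1% (OR 2.03) | 0.39 | about 169 | about 89% at 40.0% |

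The two readings therefore differ by about four percentage points of power in either direction.

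**5. Dropout arithmetic.** 240 × 0.85 = 204 and 225 × 0.80 = 180. Both agree with the plan.

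**The case against.** The strongest reply is that this is one wrong number with little consequence. If the percentages were the input, 2.03 is a misprint and neither power nor sample size changes. If 2.03 was the input, the printed claim is conservative, since power at 40% would be about 89%. The 81% figure is power for an effect smaller than the printed 16 points. All of that stands, and nothing here shows that 240 is the wrong target. What the reply does not remove is the contradiction within the sentence.

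A reader might go further and infer that the two 85% statements cannot both be right because they imply different within-person correlations. With three visits for both aims, aim 3 (90 per arm) needs 0.37, against 0.49 for aim 2 at 24% versus 40%. Aim 2 at odds ratio 2.03 needs 0.39, so one might also infer that 2.03 was the true input, run with one shared correlation. The documents do not support either step:

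- The three visits are stated for aim 2 only. Table 2 schedules surveys at 3, 6, 9 and 12 months, so self-reported PrEP use could have up to four measurements, although the 9-month contact may be a brief phone check-in.
- With four measurements, aim 3 needs about 0.44. A common correlation of 0.45 then gives about 86.5% for aim 2 (24% versus 40%) and 84.4% for aim 3, both close to 85%.
- Viral suppression and self-reported PrEP use are different outcomes in different groups, and nothing requires them to share a correlation.

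The unprinted correlation is also no fault in itself, because a journal article may leave it to the full protocol.

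**Conclusion.** The error is certain but small. The aim 2 odds ratio and percentages contradict each other: 2.11 against 2.03, or equivalently 40.0% against 39.1%, about 0.9 points. This needs no assumption beyond the definition of an odds ratio. Aim 3 is correct.

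Whether the true power differs from the stated 85% is open. The illustrative figures of 81% and 89% rest on the assumed two-sided 5% level, the pooled-variance test and exchangeable correlation over three visits. They bracket the consequence and do not show which input was used. That aims 2 and 3 may imply different correlations is not an error.

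**What to change.** Retrieve the aim 2 power calculation and see whether the proportions or the odds ratio was entered. Then print one consistent pair:

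- 24.0% versus 40.0% (16.0 points) with odds ratio 2.11; or
- 24.0% versus 39.1% (about 15.1 points) with odds ratio 2.03.

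Confirm that the 85% at n = 200 was computed for the pair printed, and restate the power if it was not. The aim 3 odds ratio needs no change.

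The cost is one corrected sentence and a look at the original calculation, with a rerun only if the 85% proves to belong to the other effect. No change of sample size follows from this point alone.

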#### Data Analysis

Aim 1 analyses are descriptive and include baseline characteristics related to sociodemographic characteristics, HIV infection, and sexual behavior of the YBLMSM and YBLTW samples across all sites as well as stratified by site. Descriptive tables with unweighted estimates and Pearson chi-squared tests for significance are used to compare age, web-use and venue attendance, and other characteristics of each recruited seed type.

To compare the efficiency of *seeds* from direct versus indirect seed selection in the recruitment of HIV-positive or at-risk youth, we use the RDS statistical package developed by Schonlau and Liebau [90]. This permits an assessment of the overlap of networks across seed types and across recruitment sites. Efficiency is assessed through recruitment diagnostics, including coupon return rate, homophily, the mean number of recruits, and recruitment depth per seed type. This approach also allows us to assess the time from recruitment activation through the achievement of target sample size and response rates. RDS weights will not be utilized in these analyses, as this aim focuses on descriptive sample proportions rather than producing population-based estimates. We will also examine the networks described by younger (aged 15-19 years) and older (aged 20-24 years) participants recruited from different *seeds* and use similar methods to understand the overlap of age groups across different networks.

The primary outcome for aim 2 is durable viral suppression (HIV viral load<200 copies/mL), and the secondary outcome is retention in HIV care (defined as documented 2 or more follow-up medical visits over 12 months, treated as a dichotomous variable). The primary outcome for aim 3 is self-reported PrEP use over 12 months in PrEP users, and the secondary outcome is self-reported condom use in PrEP nonusers. The overall approach is based on an intention-to-treat analysis with treatment assignment (eg, coached-based MEI vs SOC) being the primary independent variable for all models.

The success of the randomization process is measured by comparing the distribution of participant characteristics between the 2 groups at baseline. If the randomization process does not result in comparable groups, adjustment is made for group differences in the multivariable models. For aim 2, logistic regression is used to examine whether participants who receive MEI coach are more likely to be virally suppressed as well as retained and engaged in HIV care than participants in the SOC arm. Generalized estimating equations (GEE) are used to determine whether treatment assignment predicts differences in retention for the coached-based MEI versus the SOC groups using repeated measurements over a 12-month period. GEE is used for the longitudinal data as it adjusts for the intra-personal correlation of repeated measurements on the same individual and provides an estimate of the standard error that is robust to misspecification of this correlation structure.

For aim 3, to evaluate whether YBLMSM and YBLTW receiving coached-based MEI have greater uptake of PrEP over 12-months, a survival model is used to examine whether intervention assignment is associated with time to PrEP use. GEE is used to determine whether treatment assignment predicts differences in PrEP utilization and adherence over time for the coached-based MEI versus SOC groups using the repeated measures over the 12-month period [91]. For both aims, we explore trends in uptake and adherence to treatment or PrEP for the intervention group compared with the control group by including an interaction term between time from randomization and treatment assignment.

Going beyond the intention-to-treat approach, we will develop multivariate models stratified by age group (aged 15-19 years and 20-24 years) and include potential confounders and predictors such as prior exposure to case management and PrEP, sexual risk (low vs high), and other demographic variables. Additional models will be evaluated for possible dose-response relationships considering a measure of the level of engagement with the intervention and the frequency of app use. We will assess whether receiving coached-based MEI results in decreased substance use severity, by examining changes in mean CRAFFT scores (a measure of substance use severity) over time for the intervention group compared with the control group for each aim. CRAFFT scores will be treated as continuous dependent variables, and the models will adjust for intra-personal correlations between repeated measurements. Multivariate linear regression will be used to test for decreased severity at each follow-up visit, while controlling for identified confounders.

Modeling techniques have been selected based on the capacity to adequately handle the missingness of data. GEE models assume that the missingness is because of a missing at the random mechanism, which is a restrictive assumption. To address dropout, we use inverse probability weighting to relax this assumption of missing at random [92,93]. Other types of missing data will be handled using multiple imputations.

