##### Recruitment

Participants are recruited using RDS with targeted seed selection. As part of aim 1, we aimed to compare direct and indirect targeted seed selection methods for reaching at-risk youth (behaviorally at risk for HIV acquisition or living with HIV and virally unsuppressed). Direct seed selection consists of informational flyers directly given to youth from study staff at a clinical site or at a community-based organization or in-person event (eg, house ball, pride, or community informational session). Indirect seed selection consists of informational flyers posted at clinical sites that serve LGBTQ youth or at the offices of community-based organizations. Indirect seed selection also includes a web-based approach that consists of electronic advertisements placed on webpages and social and sexual networking sites frequented by YBLMSM (eg, Jack’d, Black Gay Chat, and Grindr; Figures 3 and 4). A link on the web-based advertisements directs potential participants to the study landing page where they can leave their information for staff to contact them about participating [56]. The staff maintain the page and rotate images frequently to maintain engagement. Staff return all web messages within 48 hours.

RDS is a chain-referral sampling method that is typically used to approximate a probability sample of populations when sampling frames are unavailable [57,58]. For the purpose of this protocol, RDS is used to recruit behaviorally at-risk youth to status-dependent RCTs. Each seed was asked to participate in the study and to invite up to 5 peers from the target population to be screened for study eligibility. Unlike other HIV research, our goal is not to approximate a probability sample to produce population-based estimates but to investigate associations with risk behaviors and to identify participants who could be enrolled in the RCTs.

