As recommended during formative research, this study uses electronic coupons (e-coupons) to facilitate the distribution of study coupons, given the challenges youth may face in physically meeting with peers to distribute paper coupons (as had been done previously). At the initial visit, a staff member meets with a participant, brainstorms about who to distribute coupons to peers, and provides instructions for the distribution of e-coupons using cell phones. The staff member provides a unique participant web link to the participant, which they then use to send their e-coupon to peers, including friends and social contacts. The link takes the participant to a page where they can see and manage the sharing of their e-coupons with peers. During the visit, the participant is asked to send their e-coupons to their peers (electronic respondent-driven sampling [eRDS] recruit) and to verify receipt. The eRDS recruit (a person receiving the e-coupon) receives a text message informing them that they have been invited to participate in a research study. The text message includes a unique numeric code, study telephone number, study site operating hours, and an expiration date (approximately 2 weeks after issuance). The recruit then contacts the study team to set up an appointment at the study site, at which point they are asked to provide their e-coupon to staff to initiate eligibility screening. The unique numeric code of the e-coupons permits the identification of linkages between *seeds* or recruiters and recruits in the data. E-coupons omit any sensitive information about participating in an HIV-related study, though *seeds* or recruiters and peers can discuss this verbally. Participants who are unable to distribute e-coupons or who choose not to use e-coupons are provided paper coupons for distribution.

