## Results

A total of 585 participants have been screened to date, with 450 (76.9%) enrolled. Recruitment monitoring showed that seed propagation was slow and reached low depths, frequently ranging from 1 to 3 waves of recruitment before stopping.

Table 3 summarizes the key demographic characteristics and reported substance use of baseline participants (N=402) and those who enrolled in aim 2 (n=36) and aim 3 (n=123). In summary, the median age was 21.6 years at enrollment, most participants identify as African American/Black (76.6%), 41 (10.2%) identify as transgender or female, 145 (41.5%) completed high school, and 145 (36.1%) had at least some college or technical education. One-quarter (97/402, 24.1%) reported having been without a place to stay in the last year, and most participants reported a history of substance use: alcohol (77.6%); cannabis (76.6%); and about a fifth reported use of other drugs including opioids, amphetamine, and cocaine (21.9%). Almost a quarter (n=100) reported engaging in transactional sex for a place to stay, money, or food. Moreover, 10% of the participants described having been forced to do something sexually (coerced sex, n=40) and 10.8% (n=43) described being forced not to use a condom during sex. Qualitative research is also ongoing. A total of 19 baseline interviews have been conducted within the 3 sites, with 9 interviews from aim 2 participants and 10 interviews from aim 3 participants.

**Table 3 table3:** Demographic characteristics and substance use at baseline for participants.

Characteristics		AMSAB^a^ participants (N=402)	Participants in aim 2 (n=36)	Participants in aim 3 (n=123)
Age (years), median (IQR)		21.6 (19.3-23.5)	22.9 (19.8-23.9)	20.7 (18.8-22.8)

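### The aim 1 chi-squared comparison by seed type does not state its unit; if recruits are included, it ignores clustering within referral chains and is anti-conservative (minor)

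*Protocol article*

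**What the plan says.** Under Clinical Trial Methods, the Data Analysis section opens with "Aim 1 analyses are descriptive and include baseline characteristics". It then adds significance tests by seed type, on unweighted estimates: "Pearson chi-squared tests for significance are used to compare age, web-use and venue attendance, and other characteristics of each recruited seed type". No allowance for dependence between participants is mentioned.

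The next paragraph gives the direct versus indirect efficiency comparison to an RDS software package: "Efficiency is assessed through recruitment diagnostics, including coupon return rate, homophily, the mean number of recruits, and recruitment depth per seed type". It also says that RDS weights will not be used, because the aim is to describe sample proportions and not to estimate population values.

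On how the sample arises, the Recruitment section for aim 1 says: "Each seed was asked to participate in the study and to invite up to 5 peers from the target population". Recruiter and recruit can be linked: "The unique numeric code of the e-coupons permits the identification of linkages between" seeds or recruiters and their recruits. The Results section reports that "seed propagation was slow and reached low depths, frequently ranging from 1 to 3 waves of recruitment before stopping".

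**The concern.** Pearson chi-squared takes its reference distribution from independent observations. Direct or indirect seeding is a property of the seed, so everyone later referred through that seed carries the same label. If friends who refer each other also tend to share age, web use or venues, a chain of several participants holds less information than the same number of unrelated people. The test does not know this, so it understates the variance of the difference between seed types.

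At stake is whether the two seeding methods are reported as bringing in different kinds of youth when the difference reflects only a few friendship chains. Several characteristics are to be tested, so the chance of at least one such report is larger than for a single test. The Discussion says the work on seed selection may inform later recruitment methods. The reason given for omitting weights concerns population estimation. It does not bear on the standard error of a comparison between seed types.

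**Working it through.** **No figure to reproduce.** The article states no significance level, number of seeds, chain size or homophily value for this comparison. What follows shows the size under stated assumptions.

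**From the article:** 402 participants (Table 3); up to 5 invited peers (stated for seeds; its use for recruits is my assumption); chains frequently of 1 to 3 waves (Results).

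**Assumed:** two-sided nominal 5%; a binary trait with 30% prevalence; seeds split evenly between direct and indirect; no true seed-type effect.

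**1. Design effect.** With mean chain size m and within-chain correlation ICC, DE = 1 + (m − 1) × ICC. The true error of a nominal 5% test is 2 × [1 − Φ(1.96/√DE)]. Example: m = 3 and ICC = 0.20 give DE = 1 + 2 × 0.20 = 1.40, 1.96/√1.40 = 1.66, and an error of 9.8%.

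| Mean chain | ICC 0.05 | ICC 0.10 | ICC 0.20 |
|---|---|---|---|
| 2 | 5.6% | 6.2% | 7.4% |
| 3 | 6.2% | 7.4% | 9.8% |
| 5 | 7.4% | 9.8% | 14.4% |
| 10 | 10.4% | 15.5% | 24.1% |

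This formula treats all chains as equal in size, so I also simulated branching chains.

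**2. Simulation, seeds and recruits pooled.** Each person brings in Binomial(5, R/5) recruits, for up to 3 waves. Chains are added until 402 participants are reached. A recruit copies the recruiter's trait with probability h and otherwise draws at random. Mean chain size is 1 + R + R² + R³; for R = 0.8 this is 1 + 0.8 + 0.64 + 0.512 = 2.95.

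| R | Mean chain | h = 0.1 | h = 0.3 | h = 0.5 |
|---|---|---|---|---|
| 0.8 | 2.9 | 6.4% | 12.5% | 17.4% |
| 1.2 | 5.4 | 7.2% | 14.1% | 22.4% |
| 1.5 | 8.1 | 7.1% | 14.7% | 26.0% |

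For mean chains of about 2, the rate is about 5-12% over the same h. With h = 0 it stays at 4-6%, so the excess comes from the resemblance.

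**3. Seeds only.** The same Pearson test on the seeds alone rejects in 4-6% of simulated trials in every setting. Nothing needs correcting on that reading.

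**4. Clustered test.** A variance clustered on the chain brings the pooled comparison back to about 5-7%.

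**5. Which row fits the trial?** Let q_k be the chance that a chain has died out by wave k, with q_0 = 0. Then q_(k+1) = (1 − R/5 + (R/5) × q_k)^5. For R = 0.8 the sequence is 0.42, 0.61, 0.73, 0.80, so without a cap 20% of chains would reach a fourth wave. The corresponding shares are 51% for R = 1.2 and 71% for R = 1.5. Chains that often stop within 1 to 3 waves therefore fit R = 0.8 or lower best. The highest figures come from growing chains cut off at wave 3.

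**The case against.** **The sentence may concern seeds only.** In the Recruitment section, direct and indirect are ways of selecting seeds, and seeds are not chain-referred. This stands as a possible reading, and the test is then valid. Two things lean the other way. The disclaimer of RDS weights for these analyses has little purpose if only seeds are tabulated. The study-measures box also says that venue data serve to examine overlap between seed networks, and venue attendance is one of the tested variables. Neither settles the unit.

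**Efficiency is judged elsewhere.** A reader might infer that the main direct versus indirect comparison rests on these p-values. It does not: efficiency is assessed by coupon return, homophily, number of recruits and depth. The chi-squared tests address only which youth each seed type brings in.

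**Resemblance is not documented.** A reader might take the planned homophily measure as evidence that recruits resemble their recruiters. It is listed as a diagnostic, with no value or expectation, so h and ICC remain assumptions. With short chains and weak resemblance the inflation is small.

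**Aim 1 is called descriptive, and an article condenses the protocol.** This lowers the weight of the point but does not remove it. The article names the test and calls for significance, so this is a stated choice and not an unreported detail.

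**Conclusion.** The point holds conditionally and is minor. The unit of analysis is unstated, and the validity of the named test depends on it. If the unit is seeds, the test is sound. If recruits are included, which is the likelier reading, the test is anti-conservative whenever recruits resemble recruiters.

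Under the assumptions above, the false positive rate is about 5-12% for chains of about 2 and about 6-17% for chains of about 3, which best match the reported propagation. It reaches about 26% only for chains of about 8 with strong resemblance. A reader might infer from that last figure that the aim 1 results are badly unreliable; the slow propagation in the Results does not support that.

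Nothing here bears on the aim 2 and aim 3 randomised comparisons, where arms are allocated to individuals within site and age strata.

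**What to change.** In the aim 1 paragraph of the Data Analysis section:

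- State whether each comparison by seed type uses the seeds alone or all participants in their chains.
- Keep the plain Pearson chi-squared test for seeds only.
- For any comparison that includes recruits, use a Rao-Scott corrected chi-squared test, or a GEE or logistic model with seed type as predictor and robust standard errors clustered on the originating seed's chain.
- Leave the estimates unweighted, as planned.

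The cost is a sentence or two of wording and a little more analysis. Chain membership can be rebuilt from the coupon codes, and the team already plans GEE with robust standard errors for aims 2 and 3. The downside is wider confidence intervals and fewer nominally significant differences.
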